## Abstract

**Background:**

There is individual variability to cardiorespiratory fitness (CRF) training, but the underlying cause is not well understood. Traditionally, a standardized approach to exercise prescription has utilized relative percentages of maximal heart rate, heart rate reserve (HRR), maximal oxygen uptake (VO_2_max), or VO_2_ reserve to establish exercise intensity. However, this model fails to take into consideration individual metabolic responses to exercise and may attribute to the variability in training responses. It has been proposed that an individualized approach would take into consideration metabolic responses to exercises to increase responsiveness to training.

**Methods:**

In this randomized control trial, participants will undergo a 12-week exercise intervention using individualized (ventilatory thresholds) and standardized (HRR) methods to prescribe CRF training intensity. Following the intervention, participants will be categorized as responders or non-responders based on changes in maximal aerobic abilities. Participants who are non-responders will complete a second 12-week intervention in a crossover design to determine whether they can become responders with a differing exercise prescription. There are four main research outcomes: (1) determine the cohort-specific technical error to use in the categorization of response rate; (2) determine if an individualized intensity prescription is superior to a standard approach in regards to VO_2_max and cardiometabolic risk factors; (3) investigate the time course changes throughout 12 weeks of CRF training between the two intervention groups; and (4) determine if non-responders can become responders if the exercise prescription is modified.

**Discussion:**

The findings from this research will provide evidence on the effectiveness of individualized exercise prescription related to training responsiveness of VO_2_max and cardiometabolic risk factors compared to a standardized approach and further our understanding of individual exercise responses. If the individualized approach proposed is deemed effective, it may change the way exercise specialists prescribe exercise intensity to enhance training responsiveness.

**Trial registration:**

ClinicalTrials.gov, NCT02868710. Registered on 15 August 2016.

**Electronic supplementary material:**

The online version of this article (doi:10.1186/s13063-016-1735-0) contains supplementary material, which is available to authorized users.

## Background

Heterogeneity in the response to exercise training first received attention in the 1980s [1] with a series of standardized studies investigating trainability of sedentary adults. Among these studies was an investigation into responses of maximal aerobic power in which it was reported that interindividual differences ranged from 5% to 88% [2]. Even though these original findings were reported over 30 years ago, substantial individual variability in response to prescribed exercise regimes remains a poorly understood phenomena. Nonetheless, it has been purported that a more individualized approach to the exercise prescription may enhance training efficacy and limit training unresponsiveness. For instance, it has been acknowledged as far back as the late 1970s that utilizing a relative percent method (i.e., % heart rate reserve [HRR]) to establish exercise intensity fails to account for individual metabolic responses to exercise [3]. Nevertheless, the relative percent concept remains the gold standard recommendation for exercise intensity [4]. It is both plausible and practical to think that an intensity set based on an individual’s threshold measurement (i.e. ventilatory threshold) will not only encourage more positive physiological adaptations, but may account for some of the variability in training responsiveness by taking into consideration individual metabolic differences. Based on an extensive search of the literature, to our knowledge, there is only one investigation that set out to determine the incidence of response based on exercise prescription using standard methods (%HRR) compared to individualized methods (threshold based) in which they found 100% of the individualized group responded in a positive manner [5]. However, this investigation had several limitations including a modest intervention duration, only reported maximal oxygen uptake (VO_2_max) changes, and sourced measurements for biological variability to use as criteria for response rate rather than testing for biological variability within the laboratory where data were collected.

A notable factor that confounds current understanding of training response variability is the absence of a set definition in the literature of how to interpret a response (i.e. what classifies someone as a responder or non-responder). Indeed, criteria to determine incidence of response for changes in VO_2_max have included classifying a fixed proportion of the lowest training response [6], absolute changes in pre- to post-intervention values [7, 8], and a change of more than one standard deviation [9]. More recently, it has been proposed that technical error (TE), the combination of day-to-day biological variability and measurement error, should be applied to categorize response rate [10]. If these values are considered for each research cohort to report incidence of response, there would be greater consistency of reporting results within the literature to provide further insight on individual variability. Moreover, interpretation of the individual variability in training responsiveness is limited due in part to the standard practice of past studies only reporting group means and standard deviations. With reporting of only the mean and standard deviation, results of the intervention may not be applicable to all since there is a lack of understanding related to the individual variability of the investigation.

This trial will be the first investigation to address the incidence of response of VO_2_max and cardiometabolic risk factors following individualized and standardized cardiorespiratory fitness (CRF) training using a specific cohort-calculated TE as the criteria for response. Similarly, this will be the first study to evaluate the efficacy of modifying the CRF training intensity prescription for non-responsive participants (based on changes of VO_2_max) to investigate subsequent training responsiveness.

### Research aims

The objective of this research is to determine the incidence of response to VO_2_max after implementation of a standardized (%HRR) and individualized (based on first ventilatory threshold [VT1] and second ventilatory threshold [VT2]) approach to exercise prescription in a community wellness program for 12 weeks. The primary measurement outcome will be VO_2_max with secondary outcomes of total cholesterol (TC), high-density lipoprotein (HDL), low-density lipoprotein (LDL), triglycerides, blood glucose, and resting heart rate (HR) and blood pressure (BP). Thus, the main research aim is to determine whether an individualized exercise prescription decreases the incidence of non-response to CRF and cardiometabolic measurements compared to the standardized approach. Similarly, another primary research aim is to determine if changing the prescription of CRF intensity for a subsequent 12-week intervention elicits more responsiveness in previously categorized non-responders (based on VO_2_max responses). A key secondary aim of this research is to establish whether there are differences in the time course changes of VO_2_max and cardiometabolic risk factors between the experimental groups every fourth week during the 12-week intervention.

## Methods/Design

The Standard Protocol Items: Recommendations for Interventional Trials (SPIRIT) guidelines [11] have been taken into consideration for the planning of this trial (Additional file 1). The overall study (Fig. 1) is a randomized control trial with participants completing a CRF training study 3 days a week for a duration of 12 weeks using a standardized (%HRR) and an individualized (based on VT1 and VT2) approach (see Additional file 2: overall SPIRIT study schedule or Tables 1, 2 and 3 for SPIRIT schedule design). If participants do not have a favorable outcome after 12 weeks (i.e. non-responders), they will complete a second 12-week intervention with a crossover design of the other exercise prescription. The protocol has been approved by the Auckland University of Technology Ethics Committee (16/264) and the Human Research Committee of the Institutional Review Board at Western State Colorado University (HRC2016-01-90R6) with data collection occurring only at Western State Colorado University.

**Fig. 1 Fig1:**
[figure not shown]
Schematic illustration of the research design

**Table 1 Tab1:** SPIRIT study calendar for the experimental group for the first 12-week intervention

			Exercise intervention				
Point of time:	Pre-intervention	Baseline	Time 0	Week 4	Week 8	Week 12	12-week analysis
Enrollment							
Recruitment	x						
Medical history	x						
Inclusion criteria	x						
Randomization			x				
Testing							
Height		x		x	x	x	
Weight		x		x	x	x	
Resting heart rate		x		x	x	x	
Resting blood pressure		x		x	x	x	
Waist circumference		x		x	x	x	
Low-density lipoprotein		x		x	x	x	
High-density lipoprotein		x		x	x	x	
Triglycerides		x		x	x	x	
Blood glucose		x		x	x	x	
Maximal exercise test		x		x	x	x	
Verification test		x		x	x	x	
3-day nutrition recall		x				x	
Analysis							
Biological variability			x				
Time course changes							x
Incidence of response							x

*SPIRIT* Standard Protocol Items: Recommendations for Interventional Trials

**Table 2 Tab2:** SPIRIT study calendar for the control group for the first 12-week intervention

Point of time:	Pre-intervention	Baseline	Time 0	Week 4	Week 8	Week 12	12-week analysis
Enrollment							
Recruitment	x						
Medical history	x						
Inclusion criteria	x						
Testing							
Height		x		x	x	x	
Weight		x		x	x	x	
Resting heart rate		x		x	x	x	
Resting blood pressure		x		x	x	x	
Waist circumference		x		x	x	x	
Low-density lipoprotein		x		x	x	x	
High-density lipoprotein		x		x	x	x	
Triglycerides		x		x	x	x	
Blood glucose		x		x	x	x	
Maximal exercise test		x		x	x	x	
Verification test		x		x	x	x	
3-day dietary recall		x				x	
IPAQ		x		x	x	x	
Analysis							
12-week changes							x

*SPIRIT* Standard Protocol Items: Recommendations for Interventional Trials, *IPAQ* International Physical Activity Questionnaire

**Table 3 Tab3:** SPIRIT study calendar (second 12 weeks) for VO_2_max non-responders after the first 12-week intervention

			Exercise intervention				
Point of time:	Pre-intervention	Baseline	Time 0	Week 4	Week 8	Week 12	12-week analysis
Pre-intervention							
Switch of experimental group	x						
Testing							
Height		x		x	x	x	
Weight		x		x	x	x	
Resting heart rate		x		x	x	x	
Resting blood pressure		x		x	x	x	
Waist circumference		x		x	x	x	
Low-density lipoprotein		x					
High-density lipoprotein		x					
Triglycerides		x					
Blood glucose		x					
Maximal exercise test		x		x	x	x	
Verification test		x		x	x	x	
3-day nutrition recall		x				x	
Analysis							
Incidence of response							x

*SPIRIT* Standard Protocol Items: Recommendations for Interventional Trials, *VO2max* maximal oxygen uptake

### Sample – experimental groups

For the experimental groups, participants will be recruited from a community-based wellness program serving the local area. The wellness program participants are either referred by local medical professionals or seek entrance into the program from peer referrals. In order for participants to be included in the study, they must meet the following inclusion criteria:30 to 75 years of ageConsidered low to moderate risk for cardiovascular disease [4]Currently sedentary (participating in less than 30 minutes of moderate intensity physical activity on at least 3 days a week)Resided at an altitude near 2300 m for at least the last 6 months

Participants will be excluded from the study if they have any signs, symptoms, or diagnosed cardiovascular, pulmonary, or metabolic disease. During the trial, participants will be asked to maintain their normal lifestyle to ensure any adaptations were due to the intervention.

### Sample – control group

Due to moral and ethical issues related to excluding participants from an exercise intervention to improve health, a control group will be recruited as a separate cohort. The control group participants must meet the same inclusion criteria and will not be allowed in the study if they meet the exclusion criteria, as previously mentioned.

### Sample size calculation

Sample size was projected with change in VO_2_max as the main outcome variable. The means and standard deviations of a previous study [5] were examined and the effect size for this research study was calculated. Assuming a power of 0.80 was needed and the calculated effect size for change in VO_2_max was 0.30, it was determined that approximately 16 participants would be needed for each group [12]. It is assumed there would be an approximate 20% dropout rate, so the aim will be to achieve 20 participants per group.

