#### Exercise intervention

After the completion of the baseline testing, participants will be randomly allocated to either the individualized or standardized arms at a 1:1 ratio using a computerized stratified minimization sequence. One of the primary investigators will have knowledge of the treatment groups to which participants have been allocated in order to interpret test results and prescribe target exercise intensities. However, this same investigator will not be involved in the implementation of the exercise training programs (to be completed by research assistants) in order to mitigate researcher bias. Participants will then be asked to come to the laboratory on Monday, Wednesday, and Friday to take part in the community wellness program and subsequent research. Upon arrival each day, participants will be asked to rest comfortably for 5 minutes in the seated position. Then, their resting BP and HR will be recorded. Following the resting measurements, participants will complete a 5-minute warm-up starting at a low and progressively increasing intensity until they are ready to begin their CRF exercise session. At this point, participants will be asked to stay within the designated HR (described in further detail below) outlined on their exercise log as determined based on their experimental group and week of experimental trial. At approximately 1/3 and 2/3 the total session time, an exercise physiologist or research assistant will record their current HR, rating of perceived exertion (scale 1–10), intensity of aerobic equipment, and any other pertinent notes. At the end of the CRF exercise session, the participant will be asked to complete a cooldown in which the exercise intensity is gradually reduced. While resistance training is not part of this proposed experiment, it is an integral part of the community wellness program and could be a confounding factor to the overall incidence of response. Therefore, all participants will be asked to complete the resistance training after the CRF training session is completed in order to have consistency among all participants. During the first 4 weeks, there will be no resistance training. During the next 4 weeks (week 4–8), there will be a learning and anatomical adaptation phase to resistance training in which proper technique and range of motion will be emphasized and participants will be acclimated to the resistance training machines. During the last 4 weeks (week 8–12) participants will complete one set of 8–12 repetitions on eight machine-based resistance training exercises and progress to two sets by the end of the 12th week [19].

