#### Time course changes

Measures of centrality and spread will be presented as mean ± standard deviation (SD) and ranges will be reported for each measure. The precision of estimates will be reported as 90% confidence limits. Baseline-dependent variables will be compared using general linear model (GLM) ANOVA and Tukey post hoc tests, when applicable. Because baseline and every fourth week program data will be available after the completion of the first 12 weeks the effect of training on CRF (VO_2_max) and cardiometabolic measurements (TC, HDL, LDL, resting BP, and resting HR) will be determined using repeated-measures GLM-ANOVA with the exercise intensity (individualized or standardized) as the between subjects factor. Between group 12-week changes will be analyzed using GLM-ANOVA and Tukey post hoc tests, when appropriate. The assumption of normality will be tested by examining normal plots of the residuals in ANOVA models and will be regarded as normally distributed if Shapiro-Wilk tests are not significant [12]. Effect sizes will be calculated using means and pooled standard deviations. Method of data analysis will be analysis by treatment administered. Only participants who complete ≥ 70% exercise training sessions and strictly adhere to target exercise intensity will be included in the statistical analysis. The probability of making a type I error will be set at *p* ≤ 0.05 for all statistical analyses.

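### The printed effect size of 0.30, power of 0.80 and 16 per group do not agree for the planned comparison of change in VO2max; 16 per arm detects about 1 SD

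*Protocol article*

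**What the plan says.** Under Sample size calculation, the protocol article sizes the trial on change in VO2max. It takes the effect from one earlier study: "The means and standard deviations of a previous study [5] were examined and the effect size for this research study was calculated". It then states: "Assuming a power of 0.80 was needed and the calculated effect size for change in VO_2_max was 0.30, it was determined that approximately 16 participants" per group would suffice, and raises this to 20 for about 20% dropout. The section names no effect-size index, statistical test, sidedness or within-person correlation, and it does not print the source means and SDs.

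The rest of the calculation has to be read from other sections:

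- Exercise intervention: "participants will be randomly allocated to either the individualized or standardized arms at a 1:1 ratio".
- Statistical analysis, Time course changes: between-group 12-week changes are compared by GLM-ANOVA, and visits at baseline and weeks 4, 8 and 12 also enter a repeated-measures GLM-ANOVA.
- Same section, on the effect-size metric: "Effect sizes will be calculated using means and pooled standard deviations".
- Same section, on alpha: "The probability of making a type I error will be set at *p* ≤ 0.05 for all statistical analyses".

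**The concern.** An effect size of 0.30 is modest on either of the two usual scales, d or f. Sixteen per group is a number normally associated with a very large effect. A reader who takes the section at face value will think that the randomised comparison has 80% power for a modest difference in VO2max change.

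The Limitations section does not correct that impression, because it raises possible underpowering only for the second, crossover part of the trial. What is at stake is the stated sensitivity of the main randomised comparison, which readers need in order to judge what the trial could have found.

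**Working it through.** **Inputs.** Power 0.80, effect size 0.30 and n = 16 per group come from Sample size calculation. Alpha 0.05 comes from the statistical analysis section, and 1:1 allocation from Exercise intervention. Two-sided testing is my assumption, since sidedness is not stated.

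**Dropout step.** 16 / (1 − 0.20) = 20. This reproduces and is not in question.

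**Trying to reproduce 16 from 0.30.** For two equal groups compared on change, the normal approximation is

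n per group = 2 (z₀.₉₇₅ + z₀.₈₀)² / d² = 2 (1.960 + 0.842)² / d² ≈ 15.70 / d².

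For two groups d = 2f, so f = 0.30 is d = 0.60. The last two columns use the noncentral t.

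| Reading of 0.30 | n, normal approximation | n, noncentral t | Power at 16 per arm |
|---|---|---|---|
| d = 0.30 | 15.70 / 0.09 = 174.4, so 175 | 176 | 13.0% |
| f = 0.30 (d = 0.60) | 15.70 / 0.36 = 43.6, so 44 | 45 | 37.6% |

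With f = 0.30 in a three-group one-way ANOVA, the need is 37 per group. One-sided testing does not close the gap: d = 0.30 needs 139 per group and d = 0.60 needs 36. With all 20 per arm evaluable, power is 15.2% (d = 0.30) or 45.6% (f = 0.30).

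**What 16 per arm can detect.** Solving the noncentral t for 80% power gives d = 1.02 with 16 per arm and d = 0.91 with 20 per arm.

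**Settings that do land near 16.** Each needs an input that the section does not give. For a repeated-measures group-by-time interaction I used noncentrality f² × N × m / (1 − ρ), where N is the total number of participants, m the number of visits and ρ the correlation between visits. The last column converts two-arm settings to SDs of change.

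| Setting | n per group | Difference in change |
|---|---|---|
| f² = 0.30, two groups | 15 | 2√0.30 = 1.10 SD |
| Interaction, f = 0.30, two groups, two visits, ρ = 0.3 | 17 | 1.2 / √(2 × 0.7) = 1.01 SD |
| Same, ρ = 0.4 | 15 | 1.2 / √(2 × 0.6) = 1.10 SD |
| Interaction, f = 0.30, two groups, four visits, ρ = 0, linear divergence | 16 | 1.61 / √2 = 1.14 SD |
| ANCOVA, d = 0.60, baseline correlation 0.8 | 17 | 0.60 / √(1 − 0.64) = 1.0 residual SD |
| Interaction, f = 0.30, three groups, two visits, ρ = 0.2 | 16 | depends on the pattern of the three means |

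In the two-visit rows, f = 0.30 means that each cell departs from additivity by 0.30 SD, so the arms differ by 4 × 0.30 = 1.2 SD in change before dividing by the SD of change, √(2(1 − ρ)). The results are also sensitive to ρ: at ρ = 0.5 the two-arm interaction needs 12 per group with two visits and 9 with four.

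**The case against.** The strongest reply is that the sample size section names no index. The pooled-SD definition stands in the analysis section and concerns how this trial's results will be reported. GLM-ANOVA and repeated-measures GLM-ANOVA are the planned analyses, and f or f² is an ordinary index for them. The cited sources are not at hand, and a journal article may condense a fuller calculation.

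This stands to a large extent. A reader might infer that 0.30 must be d and that the trial therefore has 13% power, or that no recognised calculation returns 16. The documents support neither. The 13% holds on one reading only, and several settings give 15 to 17. One of them is a two-visit interaction, which is itself a test of change.

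The reply does not rescue the section as printed. Every setting near 16 brings in an index or a correlation that is not stated, and the two-arm versions all come back to roughly 1 SD of change. If 0.30 is already defined on change, as "the calculated effect size for change in VO_2_max was 0.30" suggests, a correlation between visits brings no further gain. The article prints effect size, power and n together, so this is a mismatch between stated figures and not a detail left to another document.

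A reader might also infer that a null result would be taken as equivalence of the two prescriptions. The plan does not say so. Under Incidence of response it reports 90% confidence limits and calls an effect unclear when the interval overlaps the thresholds or the effect could be substantial in both directions.

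**Conclusion.** The concern holds in this form: with 80% power and alpha 0.05, an effect size of 0.30 does not give about 16 per group for the between-group comparison of 12-week change. The need is about 176 per group if 0.30 is d and about 45 if it is f. Power at 16 per arm is about 13% or 38% respectively. Sixteen evaluable per arm gives 80% power only for a difference of about 1.0 SD of change, and 20 per arm for about 0.9 SD.

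These figures assume a two-sided test, equal arms and a direct comparison of change. Which calculation the sponsor ran cannot be settled from the article, so it cannot be said whether the effect size was mislabelled or the sample size miscalculated. The detectable difference of roughly 1 SD depends little on that, because it also holds approximately under the two-arm settings that come near 16.

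**What to change.** In Sample size calculation:

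1. Name the effect-size index, the test, the sidedness and any within-person correlation assumed, and give the source means and SDs.
2. Correct the effect size so that it agrees with 16 per group under that test.
3. State that 16 evaluable participants per arm give 80% power (two-sided 0.05) for a between-arm difference of about 1.0 SD of change in VO2max, and 20 per arm for about 0.9 SD.
4. Give the power at 0.30 on the index actually used: about 13% at 16 per arm if it is d, or about 38% if it is f, for the direct comparison of change.

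The cost is wording only. Enrolment and the dropout allowance stay as they are; the stated sensitivity becomes less favourable.
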